#### T3 (follow-up assessments)

All tests performed at T0 will be repeated after 12 months follow-up at T3 and participants will again be questioned about the use of assistive devices, tolerated walking distance, complications and physical therapy in the past 12 months. The HOOS will also be administered at T3. Furthermore, the occurrence of trips, slips and falls will be monitored monthly between T1 and T3 using a daily calendar diary for postal use [58]. When a fall occurs, the participant has to answer additional questions on the daily calendar diary regarding the circumstances of the fall and the injuries caused by the fall. If a calendar is not returned or information is incomplete, the participant will be reminded to return the calendar or the missing information will be obtained during a telephone conversation.

### Sample size

We used the POMA [38] to perform a sample size calculation, because the POMA is a generic and widely used test to evaluate walking ability and has been associated with risk of falling [39,40]. Earlier clinical trials in which the POMA was used as an outcome measure reported mean differences of 4.0 and 3.5 POMA points between the intervention and control group [59,60]. The average standard deviations at follow-up measurements in these studies were respectively 3.8 and 4.8 POMA points. Assuming the lowest difference in mean value between groups (i.e., 3.5 POMA points), the highest standard deviation (i.e., 4.8 POMA points) and a correlation coefficient of 0.7, a sample size of 32 participants in each group is required to achieve 80% power with a two-tailed conservative alpha of 0.017 that is corrected for multiple comparisons. This sample size is based on the formula given by Twisk [61] to compare longitudinal outcome measures between groups.

We will include 126 participants who complete at least four weeks of intervention and pre- and post-intervention assessments (i.e., T0 and T1). Hence, participants who do not adhere to the protocol will be replaced to maintain a valid per-protocol assessment of sufficient power. In addition, this sample size allows for a maximum drop-out rate of 24% from T1 to T3.

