**Methods/design:**

The protocol describes a parallel group, single-blind, superiority randomized controlled trial with pre-tests, post-tests, retention-tests and follow-up. Hundred-twenty-six older adults with a recent fall-related hip fracture will be recruited from inpatient rehabilitation care and allocated to six weeks of C-Mill gait adaptability treadmill training (high-intensity, adaptive stepping), conventional treadmill training (high-intensity, repetitive stepping) or usual care physical therapy using block randomization, with allocation concealment by opaque sequentially numbered envelopes. Only data collectors are blind to group allocation. Study parameters related to walking ability will be assessed as primary outcome pre-training, post-training, after 4 weeks retention and 12 months follow-up. Secondary study parameters are measures related to fall incidence, fear of falling and general health.

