This study protocol is designed to examine the efficacy of C-Mill gait adaptability training for improving walking ability and reducing fall incidence and fear of falling in older adults residing in inpatient rehabilitation care to recover from a fall-related hip fracture, a group particularly prone to falling [6-9]. The efficacy of C-Mill gait adaptability training will not only be contrasted against usual care, comprising of exercises in strength, balance, overground walking, transfers and activities of daily living, but also against intensity matched conventional treadmill training (i.e., without visual context presented on the belt), promoting repetitive stepping. Literature on conventional treadmill training in older adults recovering from hip injury is quite scarce, but generally positive with regard to its efficacy [32,33]. Conventional treadmill training outperforms overground gait training in that regard, most likely because of the enhanced intensity of training (i.e., defined in number of steps taken per training session). Older adults with a total hip arthroplasty, for example, performed 1000-1500 steps during a conventional treadmill training session compared to 100-150 steps during an overground gait training session of similar duration [32]. We therefore hypothesize that both conventional treadmill training and C-Mill gait adaptability treadmill training result in better outcomes related to walking ability than usual care due to the enhanced training intensity, with superior effects for C-Mill gait adaptability treadmill training on gait adaptability aspects of walking given the concurrent focus on practicing gait adaptability. The present study will thus shed light on the relative importance of high versus low practice intensity and adaptive versus repetitive stepping as key ingredients for effective intervention programs aimed at improving walking ability and reducing fall risk and fear of falling in older adults recovering from a fall-related hip fracture.

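### The 3.5-point POMA difference behind the 80% power claim is supported only for intervention versus control; none is justified for adaptability versus conventional treadmill training, and the 0.017 per comparison gives away power in a three-arm trial

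*Protocol article*

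**What the plan says.** The Sample size section of the protocol article takes its effect size from two earlier trials that "reported mean differences of 4.0 and 3.5 POMA points between the intervention and control group". It adopts the smaller difference ("Assuming the lowest difference in mean value between groups (i.e., 3.5 POMA points") and "the highest standard deviation (i.e., 4.8 POMA points". It then states that with "a correlation coefficient of 0.7, a sample size of 32 participants in each group is required to achieve 80% power", using a "two-tailed conservative alpha of 0.017 that is corrected for multiple comparisons". The formula is described as follows: "This sample size is based on the formula given by Twisk [61] to compare longitudinal outcome measures between groups". Recruitment is set at 126 participants, 42 per arm, to allow up to 24% drop-out between T1 and T3.

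The section gives one difference and one power figure. It does not say which of the three contrasts they are meant for, and it gives no separate value for AT versus CT.

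The Background expects both treadmill arms to do better than UC on walking ability, with "superior effects for C-Mill gait adaptability treadmill training on gait adaptability aspects of walking". The Abstract, Background and Conclusions all list adaptive versus repetitive stepping among the questions the trial should inform.

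**The concern.** A single effect size is reasonable for three pairwise tests only if it is plausible for each of them. Here it was observed for active treatment against control, and AT versus CT is a different kind of comparison. Under Intervention program, both arms walk on the same treadmill for 15 sessions, both receive the same 15 conventional therapy sessions, and AT sessions in week 1 are run like CT sessions. The authors also expect no difference in step count between the two arms.

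The three differences are tied together, because AT-UC equals the sum of AT-CT and CT-UC. With AT at or above CT and CT at or above UC, they cannot all be 3.5 points.

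At stake is how a non-significant AT-CT result is read. In a trial described as having 80% power with no contrast singled out, such a result could be taken as evidence that adaptive stepping adds nothing. The design may simply have been unable to detect a difference of realistic size.

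Separately, splitting alpha equally over three comparisons costs power that a three-arm trial can keep without losing familywise error control.

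**Working it through.** **Inputs (Sample size section).** Difference 3.5, SD 4.8, correlation 0.7, two-sided alpha 0.017 (z = 2.387), power 80% (z = 0.842). The number of follow-ups T in the formula is not stated. I assume T = 3, since Table 1 schedules POMA at T1, T2 and T3; the Abstract gives the same time points ("Study parameters related to walking ability will be assessed as primary outcome pre-training, post-training, after 4 weeks retention and 12 months follow-up").

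**Reproducing the stated figure.** n per arm = (2.387 + 0.842)² × 2 × 4.8² × [1 + (T − 1) × 0.7] / (T × 3.5²).
- T = 3: 10.42 × 46.08 × 0.80 / 12.25 = 31.4, so 32, as stated.
- T = 1, 2 and 4 give 40, 34 and 31.
- Drop-out: 42 × 0.76 = 31.9, about 32.

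**What the ordering implies.** AT-UC = (AT-CT) + (CT-UC).
- AT-UC = 3.5 with CT in between: the smaller of the other two is at most 3.5 / 2 = 1.75.
- AT-UC = 4.0, the larger cited effect: at most 2.0.
- CT-UC and AT-CT both 3.5: AT-UC = 7, well above either cited trial.
- AT and CT both 3.5 above UC: AT-CT = 0.

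**Power under the plan's formula.** SE = 4.8 × √(2 × 0.80 / n), which is 1.073 for n = 32 and 0.937 for n = 42. Power = Φ(d/SE − 2.387).

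| True difference d | n = 32 | n = 42 |
|---|---|---|
| 3.5 | 81% | 91% |
| 2.0 | 30% | 40% |
| 1.75 | 22% | 30% |
| 1.0 | 7% | 9% |

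The difference detectable with 80% power is (2.387 + 0.842) × SE = 3.5 points (n = 32) or 3.0 points (n = 42). At 1.75 points, 80% power would need 126 per arm with data.

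**With adjustment for T0 POMA.** The variance factor becomes 0.80 − r², where r is the correlation of baseline with each follow-up. The article does not give r, so I assume 0.5 to 0.7.
- r = 0.5: factor 0.55; power at 1.75 points about 34% (n = 32) or 45% (n = 42).
- r = 0.7: factor 0.31; SE 0.668 or 0.583; power about 59% or 73%; detectable difference about 2.2 or 1.9 points.

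**Multiplicity.** With exactly three arms, any two pairwise nulls together imply that all three means are equal. The closed procedure therefore reduces to a three-arm test at 0.05 followed by pairwise tests at 0.05. Simulation with 32 per arm, compared with 0.05/3 for each test:
- Both treadmill arms +3.5: CT-UC power rises from 81% to 88%.
- Means UC 0, CT 1.75, AT 3.5: AT-CT power rises from 22% to 36% (Holm: 28%).
- Familywise error stayed at or below 5% in the scenarios simulated.

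**The case against.** A reader might infer that the 80% covers treadmill versus usual care only. The article sets no such limit. Its alpha fits three pairwise comparisons, and at a true difference of 3.5 points AT versus CT has the same 81-91% power as any other contrast. What is missing is support for that size, not the calculation.

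A reader might also infer that the adaptability hypothesis itself has only 22-30% power. That does not follow. AT superiority is hypothesised on adaptability aspects of walking, for which the article has the obstacle and dual-task walking tests and the Trail Making Test. POMA is a generic sizing outcome, and the article never predicts AT above CT on POMA specifically. This objection stands. It leaves in place that POMA is the only outcome with a power claim.

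The 1.75 points is a scenario, not a figure in the article. That also stands, although it is the largest value the smaller contrast can take when AT-UC is 3.5 and CT lies in between.

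The formula ignores baseline adjustment, which the Data analyses section says the models allow. This stands too: 22-30% is the low end, and the 3.0-3.5-point detectable difference belongs to the unadjusted formula. The article does not commit to T0 POMA as a covariate or give its correlation with follow-up.

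Finally, 0.017 appears only as a sizing assumption, the article itself calls it conservative, and Bonferroni is valid. So the multiplicity change corrects no error. But 0.017 is the only multiplicity rule the article states, and the alternative is free. Its gains depend on the scenario: in the 88% case AT-CT is zero, and if CT equals UC with AT 1.75 points higher, closed-test AT-CT power is 29% rather than 36%.

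**Conclusion.** The point holds in a limited form. The sample size is correctly computed with T = 3, and its 80% applies to any contrast whose true POMA difference is 3.5 points. That size is supported only for intervention versus control. Under the ordering AT > CT > UC, a cited-size AT-UC effect of 3.5 leaves at least one of CT-UC and AT-CT at 1.75 points or less. Power there is about 22% (32 per arm) to 30% (42 per arm) under the unadjusted formula, and about 34-73% if the analysis adjusts for T0 POMA with a baseline correlation of 0.5-0.7.

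These figures rest on three follow-ups, on the ordering, and on POMA as the outcome. They do not show that the trial lacks power for AT superiority on adaptability-specific measures, for which the article gives no power figure. The multiplicity point is a free gain in efficiency, not the repair of an invalid test.

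**What to change.** 1. In the Sample size section, state that the 80% power applies to any contrast with a true POMA difference of 3.5 points and that this size is supported only for intervention versus control. Add that, under the stated unadjusted formula, AT versus CT has 80% power only for differences of about 3.5 points (32 per arm) to 3.0 points (42 per arm). If T0 POMA will be a covariate, give the assumed baseline correlation and the detectable difference that follows from it. Commit to reporting a non-significant AT-CT result as an estimate with a confidence interval and not as no difference.

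2. Replace 0.017 per comparison with a closed procedure (three-arm test at 0.05, then pairwise tests at 0.05, which controls familywise error for exactly three arms), or with Holm, which gains less. State the choice in the Data analyses section.

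The cost is wording only, with no extra patients. The downsides are a less favourable power statement for AT versus CT and simultaneous confidence intervals that are less simple than under Bonferroni.

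### Applying 0.017 to all three pairwise POMA comparisons would give up power that a three-arm step-down test recovers at the same sample size and the same 5% family error

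*Protocol article*

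**What the plan says.** The Sample size section of the protocol article bases the calculation on the POMA. Its inputs are a between-group difference ("Assuming the lowest difference in mean value between groups (i.e., 3.5 POMA points"), a standard deviation ("the highest standard deviation (i.e., 4.8 POMA points") and "a correlation coefficient of 0.7". It concludes that "a sample size of 32 participants in each group is required to achieve 80% power" at a "two-tailed conservative alpha of 0.017 that is corrected for multiple comparisons". The plan is to include 126 participants, which is described as leaving room for 24% drop-out between T1 and T3.

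Study design sets out three arms allocated 1:1:1: usual care (UC), conventional treadmill (CT) and adaptability treadmill (AT). The Background hypothesises that "both conventional treadmill training and C-Mill gait adaptability treadmill training result in better outcomes related to walking ability than usual care", with a further advantage for AT on gait adaptability aspects of walking.

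Data analyses specifies multilevel regression for the longitudinal outcomes and names no multiplicity procedure. The 0.017 is therefore the only multiplicity rule in the article. Neither the word Bonferroni nor the number of comparisons appears beside it, but 0.017 is 0.05/3 rounded and three arms have three pairs.

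**The concern.** If the sizing alpha is carried into the analysis, each of the three pairs is tested at 0.017 whatever the other two show. With exactly three means that is stricter than control of the family error requires. If one pairwise equality is false, at most one of the other two can be true, because two true equalities would force the third. Once one pair has been rejected at 0.05/3, the remaining two therefore need no further division of alpha.

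What is at stake is power for the second and third contrasts, in a trial that wants to compare both treadmill arms with usual care and also with each other.

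**Working it through.** **1. Reproduce the plan's figure.** The inputs are difference 3.5, SD 4.8, correlation 0.7, two-sided alpha 0.017 and power 80%, all from Sample size. The number of follow-up measurements, T, is not stated there. The assessment schedule has the primary outcome measured at T1, T2 and T3, so T = 3 is assumed. The usual formula for repeated measures gives

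n = 2 (z₁₋α/₂ + z_power)² SD² [1 + (T−1)ρ] / (T δ²)

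= 2 × (2.387 + 0.842)² × 23.04 × 2.4 / (3 × 12.25) = 31.36, so **32 per group**. This matches the article. Other values of T give 40 (T = 1), 34 (T = 2) and 31 (T = 4). With 42 per arm, 126 × 0.76 = 95.8, about 3 × 32.

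**2. Power for one contrast at 32 per arm.** The variance factor is 2.4/3 = 0.8. The standard error of a difference is √(2 × 23.04 × 0.8 / 32) = 1.073, and 3.5/1.073 = 3.261. Power at 0.017 is Φ(3.261 − 2.387) = 81%. At 0.05 it is Φ(3.261 − 1.960) = 90%.

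**3. The two rules compared.**
- Single-step: every pair at 0.05/3.
- Shaffer step-down: the smallest p-value against 0.05/3; if it passes, the other two each against 0.05.

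The figures come from simulated trials with z-tests and the variance above (400,000 or more per scenario). The means are POMA points for UC, CT, AT.

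| Means | n per arm | Quantity | Single-step | Step-down |
|---|---|---|---|---|
| 0, 3.5, 3.5 | 32 | each treadmill arm vs UC | 81% | 87% |
| 0, 3.5, 3.5 | 32 | both vs UC | 70% | 82% |
| 0, 3.5, 3.5 | 42 | each vs UC | 91% | 95% |
| 0, 3.5, 3.5 | 42 | both vs UC | 85% | 93% |
| 0, 1.75, 3.5 | 32 | AT vs UC | 81% | 82% |
| 0, 1.75, 3.5 | 32 | each 1.75-point contrast | 22% | 36% |
| 0, 3.5, 5.25 | 32 | AT vs CT | 22% | 37% |

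The 42-per-arm rows assume no drop-out and are an upper bound. The 1.75 and 5.25 values are assumptions; the article gives no expected AT–CT difference.

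With pooled-variance t-tests the 32-per-arm results for (0, 3.5, 3.5) are slightly lower: 79% to 86% per contrast, and 68% to about 81% for both.

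**4. Error rates.** With no effect anywhere, the chance of any rejection is 4.4% under both rules. With AT equal to CT and both 3.5 above UC, false rejection of AT vs CT is 1.7% single-step and 5.0% step-down, the latter at the family limit but not above it. The chance of at least one rejection is the same under both rules in every scenario, because the first step is identical. Every rejection made by the single-step rule at 0.05/3 is kept.

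**The case against.** The strongest reply is that the article states 0.017 only for sizing. Sizing at the first-step alpha fits a stepwise test at analysis, since the smallest p-value must pass 0.05/3 anyway, and a statistical analysis plan that is not shown may already name one. This stands. A reader might infer that the plan commits to a fixed Bonferroni analysis, but the text does not say so. The loss arises only if 0.017 is used for every pair.

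A reader might also infer from the 70% that the trial is underpowered for its own hypothesis. The documents do not support that. The article never claims 80% for both contrasts jointly, and the Background states a scientific expectation, not a rule that both arms must win. The extra advantage expected of AT concerns gait adaptability aspects, so POMA power for AT vs CT does not measure that hypothesis. In addition, 32 per arm is what remains after the full 24% drop-out; with 42 per arm and none, the joint figure is already 85%.

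It is also tempting to call the step-down free. It needs no patients and keeps the family error at 5%. But false rejection of a truly equal pair can triple, from 1.7% to 5.0%, and simple simultaneous confidence intervals that match the tests are lost. AT vs CT is the contrast between adaptive and repetitive stepping, so the first of these should be accepted knowingly.

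**Conclusion.** The point holds as an optional improvement of low severity. The 32 per group is right for the stated alpha, taking T = 3, and nothing in the article is contradicted.

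If 0.017 were applied to all three pairs, the step-down would add about 6 points of power per contrast and 12 points for both treadmill arms at 32 per arm, when both lie 3.5 points above UC. At 42 per arm the gains are about 4 and 8 points. The gain depends on the pattern of means: with CT midway, AT vs UC gains about 1 point, while the two smaller contrasts gain about 14 points and remain poorly powered at 36%.

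The 5% family here is three comparisons on the POMA. Table 1 lists nine primary measures, and neither rule covers the other eight.

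**What to change.** Add to Data analyses, before unblinding, that the three pairwise POMA comparisons use the Shaffer step-down: the smallest p-value against 0.05/3 and, only if it passes, the other two each against 0.05. Leave the sample size as it is. Add to Sample size that 80% is power per contrast, and that T = 3 was used if that is so.

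The cost is two or three sentences, with no extra participants and no increase in the 5% family limit. Bonferroni or unadjusted intervals can be reported alongside, labelled as not matching the step-down tests. If an existing analysis plan already names a stepwise test, only the article's wording and the per-contrast statement need attention.

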## Methods/design

### Recruitment

All patients with a hip fracture admitted to residential and rehabilitation centre Zorggroep Solis, Deventer, The Netherlands will be assessed for eligibility within 3 days from admission by a physical therapist during regular intake. We aim to recruit 126 geriatric patients. Inclusion criteria are admission with a hip fracture related to falling, age ≥ 65 years, Functional Ambulation Category score 2 or higher (FAC, [34,35]), expected duration of admission ≥ 6 weeks and an ability to understand and execute simple instructions. Exclusion criteria are not being allowed to bear weight on the affected leg, moderate or severe cognitive impairments as indicated with a score below 18 at the Mini-Mental State Examination (MMSE, [36]), severe non-corrected visual impairments, contraindication to physical activity and an activity tolerance below 40 minutes with rest intervals. Patients eligible for participation will be informed of the current study by the physical therapist, both verbally and in writing. Patients who are willing to participate will be asked to give informed consent.

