### Study design

This protocol presents a parallel group, single-blind, superiority randomized controlled trial with pre-tests, post-tests, retention-tests and follow-up (Figure 2) to evaluate the relative efficacy of three intervention programs. Prior to randomization, pre-intervention assessments (T0) will be performed by one of two assessors within one week from informed consent. Subsequently, the assessor will randomly allocate (ratio 1:1:1) participants to one of three groups: 1) usual care (UC) control group, 2) conventional treadmill (CT) intervention group, 3) adaptability treadmill (AT) intervention group. We will use computer-generated block randomization with a block size of 21 participants to ensure equal group size after each block, with allocation concealment by opaque sequentially numbered envelopes that will be allocated serially to participants. An independent assessor blinded to group allocation will conduct post-intervention assessments (T1) within one week after completion of the intervention program. The same assessor will repeat these assessments 1 month later (retention assessments, T2). Follow-up assessments (T3) will be performed 12 months after completion of the intervention program. Furthermore, the incidence of trips, slips and falls will be monitored monthly between T1 and T3.

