### Data analyses

Descriptive statistics will be used to present group characteristics (e.g., sex, age, MMSE, medication use, comorbidities, side of fracture and the use of an assistive device), therapy adherence and adverse events. Baseline characteristics will be compared between groups with one-way ANOVAs. Given the explanatory objective of this study regarding the efficacy of C-Mill gait adaptability training, data will be analyzed per protocol, which implies that we will only include data of participants who completed at least 4 weeks of training and pre-intervention and post-intervention assessments (i.e., both T0 and T1). For longitudinal outcome measures (FAC, POMA, EMS, VAS, FES-I, TMT, NEADL, 10MWT, 10MWT_cognitive_, 10MWT_obstacle_, TUG, HOOS), multilevel regression analyses will be applied, which is appropriate for analyzing longitudinal data in which observations within one participant over time are correlated [61]. In addition, multilevel regression analyses account for missing values and allow baseline covariates to control for potential differences in baseline characteristics between groups [61].

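### The figure of 126 is used both for patients recruited and allocated and for completers after replacement; these agree only if nobody is replaced, so either the stated enrolment or the stated power is wrong

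*Protocol article*

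**What the plan says.** The protocol article uses 126 for two counts.

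- **Recruited and allocated.** Abstract, Methods/design: "Hundred-twenty-six older adults with a recent fall-related hip fracture will be recruited from inpatient rehabilitation care and allocated to six weeks". Recruitment: "We aim to recruit 126 geriatric patients".
- **Completers.** Sample size: "We will include 126 participants who complete at least four weeks of intervention and pre- and post-intervention assessments (i.e., T0 and T1". The next sentence adds that "participants who do not adhere to the protocol will be replaced to maintain a valid per-protocol assessment of sufficient power".

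The Sample size section also requires 32 per group and allows for 24% drop-out, counted from T1 to T3.

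Study design fixes the order of events. After the T0 assessments, "the assessor will randomly allocate (ratio 1:1:1) participants to one of three groups", and the intervention follows. Opaque, sequentially numbered envelopes are used serially, with a "block size of 21 participants to ensure equal group size after each block". Data analyses restricts the analysis to the same completers as the Sample size section: "we will only include data of participants who completed at least 4 weeks of training and pre-intervention and post-intervention assessments".

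**The concern.** Whether a participant completes four weeks of treatment and the T1 assessment is known only some weeks after the envelope is opened. Anyone replaced for non-adherence has therefore already been recruited and randomised. Under the replacement rule, the number randomised is 126 plus everyone replaced. It equals 126 only with no early loss, and a replacement rule exists because some early loss is expected.

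A reader who takes the Abstract and Recruitment at face value plans for 126 enrolments at one centre. A reader who takes the Sample size section at face value plans for more, by an amount the article does not give. If recruitment stops at 126 randomised, the 24% allowance does not cover losses before T1, and the power statement no longer describes the trial.

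**Working it through.** **Inputs from the Sample size section:** difference 3.5 POMA points, SD 4.8, correlation 0.7, two-sided alpha 0.017, power 80%, 32 per group, 126 in total, drop-out 24% from T1 to T3. **From Study design:** three arms at 1:1:1, blocks of 21. **Assumed here:** three follow-up measurements (T1, T2, T3), because the article does not state how many enter the formula; and a range of losses before T1, because it gives none.

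**Step 1. Reproduce the plan's figure.**

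n per group = 2 x [SD x (z(1-alpha/2) + z(power)) / difference]^2 x [1 + (T - 1) x rho] / T

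- First part: 2 x [4.8 x (2.387 + 0.842) / 3.5]^2 = 39.2
- Variance factor: (1 + 2 x 0.7) / 3 = 0.8
- Result: 39.2 x 0.8 = 31.4, rounded up to 32. This matches the plan.

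**Step 2. Find which count 126 fits.**

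- 126 x (1 - 0.24) = 95.8, about 96 = 3 x 32
- Conversely, 1 - 96/126 = 23.8%, the stated 24%

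The allowance starts at T1, so 126 has to be the number present at T1. That is the completer count.

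**Step 3. Number to randomise for 126 completers.** Divide 126 by (1 - q), where q is the assumed loss before T1, and round up.

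**Step 4. What remains if only 126 are randomised.**

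- Completers: 126 x (1 - q)
- Per arm at T3: n = 42 x (1 - q) x 0.76
- Power: Phi(3.5 / sqrt(2 x 4.8^2 x 0.8 / n) - 2.387)

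| Assumed loss before T1 | Randomised for 126 completers | Completers if 126 randomised | Per arm at T3 | Power |
|---|---|---|---|---|
| 0% | 126 | 126 | 31.9 | 81% |
| 5% | 133 | 120 | 30.3 | 78% |
| 10% | 140 | 113 | 28.7 | 76% |
| 15% | 149 | 107 | 27.1 | 73% |
| 20% | 158 | 101 | 25.5 | 70% |
| 30% | 180 | 88 | 22.3 | 63% |

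Put another way, with 126 randomised the tolerable loss from T1 to T3 is 1 - 96 / [126 x (1 - q)]. It falls from 24% to about 15% at q = 10% and to about 5% at q = 20%. At q = 25% only 94.5 completers are left, already below 96.

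**Step 5. Effect of replacement on group sizes.** A simulation used blocks of 21, the same non-adherence in every arm, and each replacement taking the next envelope until 126 had completed. The randomised arms differed by about 2 on average between largest and smallest, and by 7 at most, because the last block may be unfinished. Among completers, at 10%, 20% and 30% non-adherence, the mean difference was about 4, 5 and 6 and the 95th percentile was 8, 10 and 12.

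**The case against.** The strongest reply is that this is a matter of labelling. The Sample size section is coherent in itself: replacement covers losses before T1, the 24% covers losses after it, and 32 per group reproduces. All of that stands. It does not rescue the Abstract, which says 126 are allocated and not merely analysed.

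A reader might go further and infer that replacement breaks the 1:1:1 allocation or its concealment. The document does not support that. Envelopes used serially fit a replacement taking the next envelope, which keeps the sequence concealed and the randomised arms close to equal. Concealment would be at risk if replacements filled the vacated arm, but no such route is described. What next-envelope replacement does not give is equal numbers among the completers analysed, and the cost of that is modest. Take invented non-completion rates of 5%, 15% and 25% in UC, CT and AT. About 126 / 0.85 = 148 are randomised, completers number about 47, 42 and 37, and after 24% loss about 35.6, 31.9 and 28.2 remain. Pairwise power is then roughly 83% (UC-CT), 80% (UC-AT) and 78% (CT-AT).

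A reader might also infer that replacement adds selection bias. Non-completers are excluded by the per-protocol rule in Data analyses whether or not they are replaced. Next-envelope replacement changes the size of the analysed set and not how it is selected. Any objection to that exclusion belongs to the per-protocol choice, which the article states openly and ties to an explanatory aim.

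**Conclusion.** The point stands as an inconsistency in a figure on which the trial relies. The figure of 126 is sound as the number of completers and wrong as the number recruited and allocated, unless nobody is lost before T1. At an assumed early loss of 5% to 30%, enrolment is understated by 7 to 54 patients (133 to 180 against 126). If enrolment is instead held at 126, power falls to between 78% and 63%, against 81% on the same calculation with 32 per arm.

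The contradiction itself needs no assumption. Its size rests on the assumed range of early loss, on three follow-up measurements in the formula, on the stated 24% loss occurring in full after T1, and on the 3.5-point effect being unchanged. The conclusion does not extend to broken allocation or to bias from replacement.

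**What to change.** Choose one meaning for 126 and use it throughout.

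- **Keep 126 as the completer target.** In the Abstract and Recruitment, give the expected number randomised, above 126, together with the early-loss rate assumed. State that each replacement takes the next serial envelope. Say that the equal group size described in Study design refers to those randomised and not to the completers analysed.
- **Or make 126 the number randomised** (six complete blocks of 21, 42 per arm). Drop the replacement rule, and restate the power for the expected total loss from randomisation to T3.

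The first option costs a larger stated enrolment: 140 at 10% early loss, 158 at 20%. The second costs stated power: about 76% at 10% early loss and 70% at 20%, each with 24% lost afterwards. It should not be done by simply relabelling the 24% as running from randomisation, unless a total loss of that size is realistic. Either way the text change is a few sentences.
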